#### **6.4.1 Sampling Approach for Facility Catchment Areas**

Across the 5 study districts, we have identified the characteristics of interest for sampling facility catchment areas to be the district and CFL model (or SOC). To recruit our study population, we will first enumerate all high-volume health facility catchment areas within these districts, where “high volume” is defined as  $\geq 30$  pregnant women newly diagnosed with HIV infection in the catchment area within the last year. We will confirm the CFL model of interest/ SOC active in each facility catchment area prior

to data collection during the study start up phase through consultation with CFL programme managers /directors and District Health Offices (DHOs).

We will then stratify all facility catchment areas according to both district (i.e. 5 districts) *and* CFL model/ SOC (i.e. 4 total models) to create 20 “joint strata”. Within each district, we will randomly select a fixed proportion (ranging between 66% and 100%) of high-volume facility catchment areas to identify approximately **40 facility catchment areas** that will serve as study sites. Table 1 provides an example of our approach to sampling community facility catchment areas within the districts of interest. A minimum of two facility catchment areas (“clusters”) per stratum will be needed to quantify the within and between cluster variability in outcomes of interest (i.e. “rate of homogeneity”), and to provide overall variance and precision estimates. This sampling strategy serves as the starting point for recruiting the study population.

| Table 1: Illustrative sampling approach for study sites.  |                                                                   |                             |                                                             |
|------------------------------------------------------------------|-------------------------------------------------------------------|-----------------------------|-------------------------------------------------------------|
| District                                                  | CFL Model (SOC=0, Mentor Mother=1, Expert client=2, CHW=3) | Joint stratum number | Estimated Number of Sampled Facility Catchment Areas |

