| 1 (Salima, total 6 high-volume sites, 100% sampled)              | 0                                                                 | 1                           | 0                                                           |
| 1 (Salima)                                                       | 1                                                                 | 2                           | 0                                                           |
| 1 (Salima)                                                       | 2                                                                 | 3                           | 0                                                           |
| 1 (Salima)                                                       | 3                                                                 | 4                           | 6                                                           |
| 2 (Lilongwe, total 12 high-volume sites, 75% sampled)            | 0                                                                 | 5                           | 2                                                           |
| 2 (Lilongwe)                                                     | 1                                                                 | 6                           | 3                                                           |
| 2 (Lilongwe)                                                     | 2                                                                 | 7                           | 2                                                           |
| 2 (Lilongwe)                                                     | 3                                                                 | 8                           | 2                                                           |
| 3 (Mzimba North/ South, total 7 high-volume sites, 100% sampled) | 0                                                                 | 9                           | 2                                                           |
| 3 (Mzimba North/South)                                           | 1                                                                 | 10                          | 4                                                           |

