| TOTAL                                                                                                                                                               |   | 20 | 40 |
| *Due to the highly rural and dispersed population in Neno, “high-volume” will be more than 10 pregnant women newly diagnosed in the catchment area within the past 1 year. |   |           |           |

As described in further detail below (see section 6.5.1), CFL site assessments will be conducted at about 20 purposively selected facility catchment areas where MOH PMTCT services are available and where one of the three CFL models of interest, or the SOC, are being offered.

To successfully meet our nested cohort enrolment target (accounting for missing locator information, maternal death, and other enrolment barriers), we will randomly sample at least 30 HIV-positive mothers per site from a fully enumerated list of all HIV-positive women meeting eligibility criteria, and seek to recruit a final nested sample of approximately 1,200 HIV-positive mothers and their HEIs (~30 MIPs per site x ~40 sites) from across all study sites. Based on Malawi HIV Unit program data, we anticipate that about 30 randomly selected HIV-positive mothers per site will represent a sample of between approximately 15% to 100% of all HIV-positive mothers newly enrolled into PMTCT during the full cohort period at each site, depending on PMTCT client volumes at selected facility catchment areas. This nested cohort sample size will not only allow for site-specific revised estimates of patient outcomes, but will also contribute site-level data to generate overall estimates for the full cohort for each CFL model.

To arrive at projected weights for each observation in our sampling scheme—which vary across joint strata—we have made the following assumptions: 1) at the *time of construction of the full MIP cohort*, we anticipate that approximately 73% of HIV-infected mothers will be alive and in care, with 4% documented as having transferred out, stopped ART, or died, and another 23% documented as lost to

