follow-up (LTFU) to the national PMTCT/ART program (defined by the MOH as all those who have not returned to the clinic for more than 2 months after the date when they were expected to run out of antiretrovirals and are not documented as having transferred out, stopped ART, or died); 2) mortality is 30% among HIV-infected mothers who are LTFU; and 3) a coefficient of variation of 0.15 should be adequate to obtain relatively conservative projections of precision in each joint stratum. Applying these considerations to our MIP target population, we will select between 66% and 100% of high-volume sites and about 30 MIPs at each site from across the 20 joint strata to enrol our nested cohort (**Table 3**).

**Table 3:** Illustrative sampling approach for individual mother-infant pairs at facility catchment area level.

| Joint stratum number | Total high-volume catchment areas in strata | Expected catchment areas sampled (66 - 100%) | Expected Range of number of PMTCT mothers available for sampling per joint stratum | Approximate Total Mothers sampled | Approximate Mothers with complete routine care data (.73 SOC, .80 CFLs) | Approximate Mothers Needing Tracing (0.27 SOC, 0.20 CFLs) |
|----------------------|---------------------------------------------|----------------------------------------------|------------------------------------------------------------------------------------|-----------------------------------|-------------------------------------------------------------------------|-----------------------------------------------------------|
| 1*                   | 0                                           | 0                                            | 0                                                                                  | 0                                 | 0                                                                       | 0                                                         |
| 2                    | 0                                           | 0                                            | 0                                                                                  | 0                                 | 0                                                                       | 0                                                         |

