#### *6.5.2.3.2 Selecting Patients for Potential Nested Cohort Participation*

All women meeting eligibility criteria for the retrospective cohort will be eligible for random sampling and inclusion in the nested cohort, regardless of their ART status in the national program (i.e. regardless of whether they are known to be active and in care or defaulted/ lost to follow-up). At each study site, we will enumerate a complete list of study-eligible PMTCT clients from the full retrospective cohort in chronological order of the date of their PMTCT referral/ enrolment. For relatively small enumeration lists (e.g. containing fewer than approximately 50—70 clients), all clients will be included as potential participants. For larger enumeration lists, we will randomly select every second to  $n^{\text{th}}$  PMTCT client for potential participation in the nested cohort, with the interval depending on the total number of eligible mothers at the site from which to choose at least 30 participants (e.g. if there are 80 mothers available for sampling, we will select every second entry; if there are 200 mothers available for sampling we will select every fourth entry; etc.). We will continue this selection process until we enrol at least 30 nested cohort participants at each study site. It is possible that we are unable to complete study procedures (described in detail below) on the first MIPs selected at each site. In such a case, we will continue randomly sampling from the enumeration list until we reach at least 30 consenting MIPs who have completed study procedures in fulfilment of our site-based enrolment target.

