All estimates will be corrected based on the outcomes of sampled MIPs using methods established for general HIV programs. The weights for outcomes of interest will be derived from the product of the inverse probability of sampling for the facility catchment area ( $1/[0.25]$ ), and the inverse probability of sampling for the MIP (between  $1/[80/100]$  and  $1/[10/100]$  depending on the final enumeration cohort), and the inverse probability of participation given that a MIP was sampled ( $1/[P(R = 1 | W = w)]$ ).

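### The facility factor in the analysis weight is fixed at 1/0.25, but facilities are sampled at 66% to 100%, so real variation in the weights between strata is lost

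*Protocol*

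**What the plan says.** Section 7.2.2.1 applies one weight to all estimates. It is the product of the "inverse probability of sampling for the facility catchment area ( $1/[0.25"]), the inverse probability that a mother-infant pair is sampled (10% to 80%, depending on the final enumeration), and the inverse probability of participation given sampling. The facility factor carries no range or qualifier; the mother-infant pair factor does.

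The design section gives different facility fractions. Section 6.4.1 states: "Within each district, we will randomly select a fixed proportion (ranging between 66% and 100%) of high-volume facility catchment areas". It repeats this after the weighting assumptions: "we will select between 66% and 100% of high-volume sites and about 30 MIPs at each site from across the 20 joint strata". Table 1 gives the fractions by district: 100% in Salima, 75% in Lilongwe, 100% in Mzimba North/South, 100% in Neno and 81% in Zomba. Table 3 gives sites available and sites sampled by joint stratum. Section 6.4.1 also says that the projected weights differ between joint strata.

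For the second factor, section 6.4.1 expects about 30 mothers per site to be "a sample of between approximately 15% to 100% of all HIV-positive mothers newly enrolled into PMTCT". For short enumeration lists, section 6.5.2.3.2 says that "all clients will be included as potential participants".

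**The concern.** A first-stage weight should undo the facility sampling that was actually done. A single value of 4 cannot do so when the design takes every high-volume site in most strata and two-thirds or three-quarters in a few. An analyst following section 7.2.2.1 as printed would give a woman from a stratum where a third of the sites were left out the same facility weight as a woman from a fully sampled stratum.

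At stake is the mix of strata behind each estimate: by model, for CFL pooled, and for the CFL versus standard-of-care (SOC) contrast on which the study is powered. If outcomes differ between the sub-sampled strata and the others, the estimates move. The second factor has a similar fault, because its printed range excludes a probability of 1, which the design allows.

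**Working it through.** **Inputs.** Table 3: sites available N, sites sampled n, and the range of mothers per stratum, whose midpoint is M. Table 1: district totals and sampled sites.

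**1. Can 0.25 be reproduced?** The facility probability is n/N.

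| Level | n/N | Inverse |
|---|---|---|
| Stratum 6 | 3/4 = 0.75 | 1.33 |
| Stratum 18 | 2/3 = 0.67 | 1.50 |
| Stratum 19 | 6/9 = 0.67 | 1.50 |
| Other ten non-empty strata | 1.00 | 1.00 |
| Table 3 overall | 40/45 = 0.89 | 1.125 |
| Lilongwe, Table 1 | 9/12 = 0.75 | 1.33 |
| Zomba, Table 1 | 13/16 = 0.81 | 1.23 |

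None gives 0.25. A weight of 4 on 40 sites would imply 4 × 40 = 160 sites; Table 3 lists 45.

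**2. What cancels.** A weighted proportion is Σwy/Σw, so multiplying every w by the same constant leaves it unchanged. Risk differences and risk ratios are built from such proportions. Only the missing relative variation matters.

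**3. Relative under-weighting.** The printed factor divided by the true factor is 4/1 = 4.0 in fully sampled strata, 4/1.33 = 3.0 in stratum 6 and 4/1.5 = 2.67 in strata 18 and 19. Relative to the rest, that is 1 − 3.0/4 = 25% and 1 − 2.67/4 = 33% too low.

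**4. Change in stratum shares.** This assumes that the other two factors are right. The mothers column of Table 3 can be read in two ways:

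- Reading A, mothers at sampled sites: correct mass is M × N/n; as written it is proportional to M.
- Reading B, mothers at all sites in the stratum: correct mass is M; as written it is proportional to M × n/N.

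Midpoints:

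- Expert client: strata 7, 11 and 19 = 175, 350, 1,000.
- Mentor mother: strata 6, 10 and 18 = 450, 150, 175.
- Community health worker (CHW): strata 4, 8, 16 and 20 = 350, 80, 75, 150 (sum 655).

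| Share | A: correct → as written | B: correct → as written |
|---|---|---|
| Stratum 19 in expert client | 1,500/2,025 = 74% → 1,000/1,525 = 66% | 1,000/1,525 = 66% → 667/1,192 = 56% |
| CHW in pooled CFL | 655/3,692.5 = 18% → 655/2,955 = 22% | 655/2,955 = 22% → 655/2,451 = 27% |
| Strata 6, 18, 19 in pooled CFL | 2,362.5/3,692.5 = 64.0% → 1,625/2,955 = 55.0% | 1,625/2,955 = 55.0% → 1,121/2,451 = 45.7% |

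**5. Conversion to outcome bias.** Bias = (change in share) × (outcome gap between partly and fully sampled strata). The protocol gives no such gap, so it is assumed. For the pooled CFL estimate:

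- 10-point gap: reading A, 0.090 × 10 = 0.9 points; reading B, 0.093 × 10 = 0.9 points.
- 5-point gap: about 0.45 points on either reading.

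The target difference in section 6.4 is 8 points.

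**6. Mother-infant pair factor.** The analysis section prints 10% to 80%, section 6.4.1 says 15% to 100%, and section 6.5.2.3.2 takes everyone on short lists (probability 1). In Table 3, stratum 16 plans 90 mothers from 50 to 100, which is at least 90/100 = 90% and above the printed maximum.

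**7. Site counts (minor).**

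- Lilongwe: Table 1 heads the district "2 (Lilongwe, total 12 high-volume sites, 75% sampled"), but Table 3 has 2 + 4 + 2 + 2 = 10 sites.
- Mzimba: Table 1 heads it "3 (Mzimba North/ South, total 7 high-volume sites, 100% sampled"), but its rows sum to 2 + 4 + 2 = 8.
- Stratum 18: 3 sites sampled in Table 1, 2 in Table 3.
- Table 1 rows sum to 6 + 9 + 8 + 5 + 13 = 41, against a printed total of 40.

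**The case against.** The strongest reply is that the method is right and one parenthetical number is wrong. The factor is defined in words as an inverse sampling probability, and section 6.4.1 says that weights vary between strata, so a careful analyst would probably substitute the realised fractions. That is fair, and it limits the severity. But the number is printed without qualification beside a factor that is given a range, so it does not read as a placeholder.

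A reader might infer that every result is inflated about threefold, since with Table 3 midpoints (reading A) the weighted cohort is 4 × 3,230 = 12,920 women against about 3,968. The documents do not support that. The planned outcomes are proportions, medians, risk differences and risk ratios, no population total is among them, and the common factor cancels.

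A reader might also infer that only mentor-mother and expert-client strata are affected. That holds on Table 3, where every SOC and CHW stratum is fully sampled. If the fraction is set by district, as the text of section 6.4.1 says, SOC and CHW strata in Lilongwe and Zomba are sub-sampled too.

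Two further points stand in part. Adjusted models control for district, so adjusted ratios should be less affected; the weighted proportions, risk differences and unadjusted ratios get no such protection. Tables 1 and 3 are labelled illustrative, so their mismatches do not matter once weights come from the realised draw.

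**Conclusion.** Wrong as written; should be fixed. The value 0.25 contradicts the 66% to 100% design whether read by stratum, by district or overall. The consequence is confined to the flattened 1.0 to 1.5 variation, which shifts weight away from the sub-sampled strata.

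The likely effect is modest: about 0.9 points on the pooled CFL estimate for an assumed 10-point gap between partly and fully sampled strata, scaling in proportion to that gap. The size rests on Table 3's illustrative midpoints and stratum fractions. The stratum shares depend on how the mothers column is read, but the direction is the same on both readings. The mother-infant pair range is a second, smaller contradiction in the same sentence, and the site-count mismatches are minor.

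**What to change.** In section 7.2.2.1:

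- Replace 1/0.25 with (eligible high-volume sites in the joint stratum)/(sites sampled in it), from the realised draw.
- Replace the 10% to 80% range with (eligible women listed)/(women drawn) at each site, allowing 100%.

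In section 6.4.1:

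- State whether the facility fraction is fixed by district or by joint stratum.
- As a minor correction, reconcile the site counts in Tables 1 and 3 for Lilongwe, Mzimba, stratum 18 and the Table 1 total.
- Say whether the mothers column of Table 3 counts sampled sites or all sites.

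The cost is a corrected sentence and table edits. No fieldwork changes.

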#### *7.2.2.2 90-90-90 Virtual Survey Analysis*

Using data from the full retrospective cohort, enriched by nested cohort data, we will calculate HIV care cascade indicators for MIPs and compare results across CFL models/SOC according to established UNAIDS 90-90-90 definitions (i.e. 90% of women and infants know their HIV status; 90% of HIV-infected women and infants are sustained on ART; and 90% of women and infants on ART achieve viral suppression). The following 90-90-90 indicators will be calculated and presented together with their associated 95% confidence intervals (CIs):

Proportion of women who know their HIV status (i.e. “Known Maternal HIV status”): For this indicator examining the first step of the HIV care cascade (i.e. the “first 90”), we will define our denominator as the number of pregnant women with a recorded ANC or Maternity Department visit in the 12 months preceding the evaluation date (e.g. the last day of study activities in the targeted district). For the numerator, we will calculate the number of pregnant women with either a documented negative HIV test result in ANC or Maternity within the last 12 months (of the evaluation date) or documented positive HIV test/ evidence of being HIV-positive before the evaluation day (e.g. a women is known to be receiving ART).

Proportion of infants who know their HIV status (i.e. “Known Infant HIV status”): For this indicator, we will define our denominator as the number of HIV-exposed infants enrolled in the national HIV Care Clinic follow-up program or registered in the MOH EID testing logbook in the 12 months preceding the evaluation day (e.g. the last day of study activities in the targeted district). For the numerator, we will ascertain the number of infants with either a documented negative DNA PCR or rapid HIV test result within the last 12 months (of the evaluation date) or documented positive HIV test/ evidence of being HIV-positive before the day of evaluation (e.g. infant is known to be on ART).

Proportion of women receiving anti-retroviral therapy (i.e. “Maternal ART Initiation”): For this second step of the HIV care cascade (i.e. “the second 90”), we will calculate the proportion of HIV-infected pregnant and breastfeeding women initiating ART during the 12 months preceding the evaluation day among all PMTCT clients with a documented positive HIV test/ evidence of being HIV-positive before the day of evaluation.

Proportion of infants/ young children receiving anti-retroviral therapy (i.e. “Infant ART Initiation”):

Similar to the related maternal indicator, for this infant ART initiation indicator, we will calculate the proportion of HIV-infected infants/ young children initiating ART during the 12 months preceding the evaluation day among all infants with a documented positive HIV test/ evidence of being HIV-positive before the day of evaluation.

Proportion of PMTCT mothers and infants/young children who started ART and have a suppressed HIV

viral load (“Viral suppression”): Using viral load test result data, we will calculate and present separately the proportion of ART-initiated, HIV-infected mothers and ART-initiated HIV-infected infants/ young children who achieved viral suppression. For this final step of the cascade (i.e. the “third 90”), we will use the numerators from the maternal and infant ART initiation indicators for our respective denominators, and will assess the subset of these denominators with documented suppressed viral load test results within 12 months of the evaluation day. We will define viral suppression using a number of established thresholds for HIV-1 viral load, including less than 20 copies/ ml (the lower limit of detection for VL testing performed on plasma collected by venipuncture), less than 550 copies/ml (the lower limit of detection for VL testing performed on DBS) and less than 1,000 copies/ml (the definition of viral suppression used in the recent MOH Malawi Population-Based HIV Impact Assessment).

*7.2.2.3 Maternal IDI Data*

For qualitative data, the same analytical approach will be employed as described for Objective 1 above, except that we will search for patterns in the data that help explain client experiences with CFL model services and navigating the PMTCT care continuum for mothers and their children.

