## 6.0 Methodology

### 6.1 Study Design Overview

We propose to rigorously define and compare three widely adopted models for community-facility linkage with each other and the standard of care using a mixed methods approach involving both quantitative and qualitative data collection.

For the quantitative component, we will first use stratified random sampling to select facility catchment areas in 5 Malawi districts where implementing partners have focused PMTCT programming. We will then visit each selected area to construct a retrospective cohort of HIV-infected women who entered the national PMTCT program and received CFL services or the SOC between July 1, 2016 and June 30, 2017. These dates have been chosen to align with the latest change to Malawi HIV guidelines supporting universal “test and treat” strategy, which became national policy on April 1, 2016 and reached stable rolled out on July 1, 2016. Using existing data, we will gather individual-level retrospective data on each woman and her infant from PMTCT enrolment through the child’s second birthday. Next, we will enrich these data using an epidemiological sampling method designed to overcome the limitations traditionally associated with retrospective data (e.g. missing data, outcome misclassification, etc.). In this second stage, we will randomly select a sample of women from our full

cohort to create our nested cohort. These women will complete a questionnaire about their experiences with CFL models and services, undergo viral load testing, and have their children ages 12–24 months receive HIV testing. Such prospective data collection will enable us to confirm primary outcomes, fill in missing data, and improve study data quality more generally.

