## 6.3 Study Population

We will begin our study by reviewing existing data from a generalizable sample of women (and their infants/ young children) from selected facilities in the 5 districts meeting the following eligibility criteria:

- Newly diagnosed or having documented evidence of HIV infection between July 1, 2016 and June 30, 2017 in selected health facilities;
- Documented referral to or enrolment in Malawi's PMTCT/ ART program;
- Pregnant (at any gestational age) or breastfeeding at the time of HIV diagnosis/ positive HIV status identification;
- $\geq 16$  years of age at the time of PMTCT referral/ enrolment (includes adults and emancipated minors according to Malawi law);
- Received Antenatal or PMTCT services at a facility catchment area served by a CFL model of interest or SOC.

Existing, routine data for these women and their infants will form the basis for our full retrospective cohort. From these data, we will randomly select women and their infants (i.e. mother-infant pairs) to participate in the nested cohort.

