## **7.2.2 Analysis Plan for Objective 2 & 2a**

### **7.2.2.1 Cohort Data**

We will calculate maternal retention in care as the proportion of mothers alive and in care at 6, 12, and 24 months post-ART initiation among all eligible women at the start of the cohort. We will also calculate median days from PMTCT enrolment to ART start to examine the effects of CFL models on time to ART initiation. We will look for differences in the delay of ART initiation across the CFL models and SOC using the Aalen-Johansen estimator to account for the competing event of death. We will report crude HEI mortality at 12 and 24 months as part of our survival analysis. We will define infant 12-month HIV free survival as the proportion of HEIs alive with a negative 12-month HIV-rapid test among all infants enrolled in the HEI birth cohort. Similarly, we will define infant 24-month HIV free survival as the proportion of HEIs alive with a negative 24-month HIV-rapid test among all infants enrolled in the HEI birth cohort. We will use Kaplan Meier techniques to compare infant HIV-free survival at 12 and 24 months across the 3 CFL models and SOC accounting for informative censoring and differences in baseline patient characteristics between the models using inverse probability weights. We will censor all survival outcomes on the last date of field activities in a given district (most likely between February 1, 2018 and April 30, 2019, depending on the district), the date of transfer, or the date of the last clinical encounter, as appropriate.

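### The second 90 counts only ART starts in the 12 months before the evaluation day against all known HIV-positive clients, and the third 90 inherits that truncated group as its denominator

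*Protocol*

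**What the plan says.** Protocol section 7.2.2.2 sets out the 90-90-90 indicators. Their stated data source is "Using data from the full retrospective cohort, enriched by nested cohort data". Section 6.1 defines that cohort as women who entered the national PMTCT programme and "received CFL services or the SOC between July 1, 2016 and June 30, 2017". The eligibility criteria in section 6.3 use the same dates and admit women already known to be HIV-positive as well as new diagnoses.

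The section words the second target as "90% of HIV-infected women and infants are sustained on ART". The maternal indicator meant to measure it is the proportion of "women initiating ART during the 12 months preceding the evaluation day among all PMTCT clients with a documented positive HIV test" or other evidence of infection before the evaluation day. The infant indicator repeats this form. For the third target, "we will use the numerators from the maternal and infant ART initiation indicators for our respective denominators".

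The evaluation day is given only by example, as the day study work ends in the district. Section 7.2.2.1 expects that day "most likely between February 1, 2018 and April 30, 2019, depending on the district". Section 6.5.2.2 gives another range for administrative censoring, from end 2017 to end 2018.

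**The concern.** Numerator and denominator cover different periods. A woman who started ART more than 12 months before the evaluation day stays in the denominator as a known positive client, but she cannot enter the numerator however well she has done. The cohort was enrolled in a fixed year that ended well before most of the expected closing dates, so this could affect most of its members, or all of them.

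Three things are at stake.

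- The second 90 would be compared with a 90% benchmark that it could not reach even with complete ART uptake.
- The indicator measures recent initiation, while the section's own wording of the target is about staying on ART.
- The third 90 would be calculated on a small or empty group, and that group leaves out the women for whom the study itself obtains later viral loads.

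**Working it through.** The protocol states no expected value for these indicators, so there is no figure to reproduce. The check is a calendar overlap.

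**Inputs**
- Cohort entry: 1 July 2016 to 30 June 2017, 365 days (sections 6.1 and 6.3).
- Evaluation day E: end of field work in the district (example in section 7.2.2.2), 1 February 2018 to 30 April 2019 (section 7.2.2.1). The end-2017 date in section 6.5.2.2 is used as a sensitivity case.
- Lag L from entry to ART start: 0 days in the base case, because section 6.5.2.3.7 describes prompt initiation in routine care. Lags of 30 and 90 days are used as sensitivity cases.
- Assumption: entry is spread evenly over the year.

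**Formula**

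Share = (days d in the entry year with E − 12 months ≤ d + L < E) / 365. If every cohort woman starts ART, this share is the highest value that the second 90 can take. It is also the fraction of the cohort left as the third-90 denominator.

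**Base case, L = 0**
- E = 1 February 2018: entries from 1 February to 30 June 2017 count, 28 + 31 + 30 + 31 + 30 = 150 days; 150/365 = 41%.
- E = 30 April 2018: 1 + 31 + 30 = 62 days; 62/365 = 17%.
- E = 30 June 2018: 1 day; 1/365 = 0.3%.
- E = 1 July 2018 or later: 0 days; 0%.

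**Sensitivity**

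| Evaluation day | L = 0 | L = 30 days | L = 90 days |
|---|---|---|---|
| 31 Dec 2017 | 182/365 = 50% | 212/365 = 58% | 272/365 = 75% |
| 1 Feb 2018 | 150/365 = 41% | 180/365 = 49% | 240/365 = 66% |
| 30 Apr 2018 | 62/365 = 17% | 92/365 = 25% | 152/365 = 42% |
| 1 Jul 2018 | 0% | 30/365 = 8% | 90/365 = 25% |
| 31 Dec 2018 | 0% | 0% | 0% |

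The section 7.2.2.1 range holds 454 possible closing dates. Of these, 304 (1 July 2018 to 30 April 2019) give zero overlap at L = 0, and 304/454 = 67%. Women already on ART when they entered the cohort would lower every figure further.

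**The third 90, without any assumption on entry or lag**

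Suppose a viral load is taken on day V, at least 12 months after ART start S, with V no later than E. Then S ≤ V − 12 months ≤ E − 12 months. Apart from the boundary day itself, that woman started ART before the window opened. She is outside the second-90 numerator and so outside the third-90 denominator. Section 7.1 places the study's own viral loads at 12 to 24 months after ART start, and the routine programme adds a 24-month test. Those results cannot contribute.

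**Comparison with section 7.1**

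The secondary outcome on the proportion of HIV-infected clients started on ART has no 12-month window. The protocol therefore holds two definitions of nearly the same quantity, which would give very different values.

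**The case against.** The strongest reply is that the figures rest on an illustrative date and a worst-case lag. The evaluation day is introduced only as an example, and an analysis plan that is not at hand could set another. Section 6.5.2.2 allows closure at end 2017, and time from enrolment to ART is itself an outcome, so the lag is not known to be zero. All of this stands, and it is why the sensitivity table is needed. It softens the percentages but does not remove the fault. No other date is offered, even the mildest case tabulated (end 2017 with a 90-day lag) misses a quarter of ART starts, and the viral-load exclusion holds for any evaluation day on or after the test.

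It can also be said that section 6.5.2.1 describes the cascade as running through ART initiation, so the conflict with being sustained on ART is one of wording. That is fair as far as it goes, but an initiation indicator would still need matching periods in numerator and denominator.

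Some stronger readings are tempting and are not supported.
- A reader might infer that the first 90 must equal 100% because the cohort contains only HIV-positive women. Section 7.2.2.2 defines that indicator on all pregnant women with an antenatal or maternity visit and counts documented negative tests, so this does not follow.
- A reader might infer that closing date is tied to CFL model, since Table 1 shows only CHW sites in Salima and Neno. That table is illustrative, CHW sites also appear in Lilongwe and Zomba, and no closing date is given for any district.
- A reader might carry the maternal percentages over to infants. Infants can be born after June 2017 and tested late, so their ART starts fall later. Their definition has the same flaw, but its size has not been computed.

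**Conclusion.** The definitions in section 7.2.2.2 do not measure what they are meant to measure and should be corrected. With even entry, ART at entry and the example evaluation day, the maternal second 90 cannot exceed about 41% at the earliest close in section 7.2.2.1, 17% at 30 April 2018, and 0% from 1 July 2018, when the third-90 denominator is empty. An end-2017 close raises the ceiling to about 50%; a 90-day lag raises it to 66% at a 1 February 2018 close. The value is thus governed by when field work ends rather than by ART coverage, and comparison with the 90% benchmarks is not meaningful.

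The exclusion from the third 90 of women whose viral load was taken 12 or more months after ART start depends on none of these assumptions.

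This is a should-fix point. A reader might infer that the main result is compromised. It is not: these are secondary cascade indicators, and 12-month maternal retention and the sample size do not use them. ART initiation and viral suppression are also analysed elsewhere in the protocol without this window.

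**What to change.** - **Second 90:** remove the 12-month initiation window. Define it as cohort women on ART at the evaluation day, or at a fixed time after PMTCT entry, divided by all HIV-positive cohort women. A fixed time has the advantage that districts with different closing dates are compared at equal follow-up.
- **Third 90:** define it as women with a suppressed viral load, at each of the thresholds already planned, divided by women on ART as defined for the second 90.
- **Infants:** apply the same alignment of numerator and denominator to the infant ART and infant suppression indicators.
- **Evaluation day:** state it as a rule instead of an example.

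The cost is rewording the maternal ART, infant ART and viral suppression definitions in section 7.2.2.2. ART start dates, care status and viral loads are already to be collected under sections 6.5.2.2, 6.5.2.3.5 and 6.6.3, so the change should need no new data collection. The sample size does not change. With the maternal window removed, every cohort ART start up to the evaluation day can be counted, whatever the closing date.
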